### Measures

Through this study, we are collecting a variety of different measures to help determine the feasibility and acceptability of utilizing this approach in a primary care setting, including: *Patient Participant Characteristics*, *Blood Pressure*, and *Medication Adherence*.

#### Patient Participant Characteristics

At baseline, we administer an investigator-developed survey to assess patient participant demographics, health status, HTN history, medication use, and other characteristics.

#### Blood Pressure

At both baseline and 12-week follow-up, patient participant BP is assessed in the clinic by a manual BP reading taken by a trained study staff member or clinic staff. In addition, home BP readings will be downloaded from the BPTrack Secured Cloud at the conclusion of the study for further analysis.

#### Medication Adherence

At baseline and the 12-week follow-up, we assess medication adherence with two different measures: the ARMS and pill counts. The ARMS is a 14-item instrument that consists of two sub-scales that assess taking medications as prescribed, and refilling medications on schedule. The ARMS has been validated for use in a population with chronic disease and has been shown to have good performance characteristics among individuals with low literacy levels [20]. Upon enrolling in the pilot study, all patient participants are instructed to save all pill bottles for antihypertensive medications, even if empty, and bring them to the follow-up assessment. Patient participant HTN medications are identified from the patient’s medical record. Information required for the pill count calculation is recorded from each prescription label including: drug name, strength, and dosage form; instructions for use; quantity dispensed; and dispensing date. Pill count adherence is determined by the following formula, [19]:

% adherence = (quantity dispensed - quantity remaining)/([prescribed # tablets/day] x [# days between dispensing date and interview]) x 100

### BPTrack and BPTrack Pharm Utilization

At the conclusion of the study, BPTrack and BPTrack Pharm utilization for patient and clinical pharmacist participants will be documented through log file analysis, with specific focus on the number of patient participant home BP readings, as well as the frequency and duration of participant use of the BPTrack and BPTrack Pharm apps.

### Health Care Utilization

Patient participant health care utilization will be conducted through a retrospective chart review of enrolled individuals in order to document the number and reason for primary care visits during the course of this study, including the frequency and nature of contacts with the clinical pharmacist (phone or in-person), with a primary care physician at the recruiting clinic, and the Emergency Department at the academic medical center.

### Patient Participant Perceptions

At the conclusion of the 12-week study period, we will conduct an investigator-developed survey focused on patient participant perceptions of BPTrack including ease of use, usefulness, impact on health outcomes, and satisfaction. We will also conduct an open-ended interview using a standardized script to elicit additional qualitative feedback.

### Key Stakeholder Utilization and Perceptions

At the conclusion of this pilot study, we will conduct an in-depth interview with the clinical pharmacist involved in this study to better understand perceptions of the system from a clinical perspective. Moreover, throughout the course of the pilot study, the pharmacist has been asked to maintain detailed logs of the time spent using the app, time spent monitoring and following-up with patient participants, and perceptions of the program. These logs will be collected and analyzed in order to document the personnel needs to maintain such a program. We will also conduct key stakeholder interviews with clinic medical directors, primary care physicians, health system administrators, and information technology personnel at the recruiting site and other affiliated clinical sites, to identify potential barriers to broader intervention dissemination, as well as strategies to overcome those challenges.

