### Sample

We are enrolling up to 25 patient participants for this pilot study. To be eligible for participation, enrollees must be ≥18 years of age, have a smartphone compatible with the mobile intervention, have been previously diagnosed with HTN, have uncontrolled HTN (SBP >140 mmHg and/or DBP >90 mmHg on repeat measurements), be under the care of a primary care physician at the recruiting clinic, be taking at least one antihypertensive medication, and be English-speaking.

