### Procedures

Any individual patient at the recruiting site who expresses interest by calling the study hotline is subsequently screened by phone. Once screened as eligible, patient participants are scheduled for an informed consent and baseline data collection appointment with study staff at the recruitment site, or another affiliated space. These visits take approximately 90 minutes to complete.

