**Figure 4 figure4:**
[figure not shown]
BPTrack Pharm individual screen.

After baseline data collection is complete, study staff help patient participants download the intervention app onto their smartphone, and train them on how to use the app. Participants are also given a Bluetooth-enabled BP monitor to take home, and are instructed on how to use it, as well as how to sync it to BPTrack. All BP monitors are checked before the patient participant leaves the baseline data collection visit, and are tested against a manual BP reading taken by a trained study staff member. Although we are not calibrating the home BP monitors, we do look to see how well their readings compare with the manual BP readings. Once enrolled in the study, the clinical pharmacist sees patient participants as needed for ongoing HTN management.

Patient participants are also instructed on the BP monitoring protocol that we will adhere to in this study, and are instructed to take three consecutive BP readings twice daily, at varying times across days. Prior to BP monitoring, patient participants are instructed to: go to the bathroom before taking their BP, if needed; keep their arm at heart level by resting it on a table during monitoring; sit in a chair with a back, with feet flat on the floor for at least five minutes prior to monitoring; avoid tobacco, caffeine, or alcohol for 30 minutes prior to BP monitoring; avoid taking their BP immediately after exercise, when emotionally upset, or in pain; and to avoid talking while taking their BP.

In the event that a patient participant has an SBP >160 mmHg, SBP <100 mmHg, DBP >100 mmHg, or DBP <60 mmHg, they are instructed to wait five minutes and then recheck their BP using the previously described protocol. Patient participants are also instructed that if BP readings exceed these critical thresholds for three days in a row, they should contact the clinic. Finally, patient participants are instructed to call the clinic immediately if they are experiencing symptoms of dizziness, chest pain, severe headache, or visual changes.

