### Limitations

Perhaps the largest limitation of this pilot study is our limited sample size, which was chosen due to the pragmatics of recruitment and budgetary constraints. As highlighted by Leon et al, “the primary role of a pilot study is to example the feasibility of a research endeavor” [21]. Our intended sample size is large enough to satisfy the rule of thumb of 12 participants per group (set forth by Julious et al [22]) as appropriate for guiding sample size selection for pilot studies. Although we may not have adequate power to detect effects, this is a true feasibility trial in which we will be able to obtain preliminary data to support and plan for future implementations. Feasibility will be assessed on many different levels, including the feasibility of using BPTrack amongst our target population, within the primary care setting, and within the health system. In addition, the lack of a control or other comparison group is a limitation of our study design; however, given that this is a pilot study to preliminarily investigate the use of this approach in a clinical setting, our single group design is warranted. Future work should seek to incorporate a more robust research design.

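### Personnel needs are to be documented from the pharmacist's logs, but study staff do the onboarding and no plan to record their time is stated (minor)

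*Protocol article*

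**What the plan says.** Under Key Stakeholder Utilization and Perceptions, the Protocol article has the pharmacist keep "detailed logs of the time spent using the app, time spent monitoring and following-up with patient participants, and perceptions of the program". The use of these records is then fixed: "These logs will be collected and analyzed in order to document the personnel needs to maintain such a program". No other data source in the article is tied to personnel needs.

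Under Methods, Procedures, the work of getting each patient started belongs to other people. After baseline data collection, "study staff help patient participants download the intervention app onto their smartphone, and train them on how to use the app". Participants are also shown how to use the monitor and sync it. The monitors are checked before the participant leaves and "are tested against a manual BP reading taken by a trained study staff member". The abstract's Methods paragraph likewise places installation and app instruction within the baseline visit. On the consent and baseline appointments, Procedures says: "These visits take approximately 90 minutes to complete". It does not divide that time among tasks.

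Under Limitations, feasibility is to be judged among the target population and also "within the primary care setting, and within the health system".

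**The concern.** Staffing is central to whether a primary care clinic can run this programme, and the pilot is meant to inform a larger roll-out. The planned staffing record follows one person. Installation, training and monitor set-up recur with every new patient, and here research personnel absorb them. A clinic adopting BPTrack would have to find someone to do whatever part of that work it keeps.

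If the personnel result comes from the pharmacist's logs and is presented as what the programme needs, it leaves out a category of labour and makes the programme look lighter to staff than it is. The gap arises at data collection: minutes not recorded at the time can later only be estimated.

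**Working it through.** The article states no personnel figure (hours, full-time equivalents or caseload), so there is nothing to reproduce. The check compares tasks with the sources that could record them, then uses assumed times to show the possible scale.

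**1. Who does the work, and what records it**

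| Work | Done by | Planned time record |
|---|---|---|
| App use, monitoring, follow-up | Pharmacist | Pharmacist's logs; app log files for BPTrack Pharm use |
| App installation and training | Study staff | None stated |
| Monitor instruction and syncing | Study staff (same visit) | None stated |
| Monitor check against manual reading | Study staff | None stated |

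Three other planned sources might be thought to fill the gap:

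- The log files (BPTrack and BPTrack Pharm Utilization) capture use of the two apps, not staff time spent setting them up.
- The chart review (Health Care Utilization) covers the frequency and nature of pharmacist contacts and other visits, not onboarding minutes.
- The stakeholder interviews concern barriers to dissemination and ways round them. They may bring out set-up burden as opinion but do not measure it.

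**2. What the visit length can and cannot show**

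Inputs: up to 25 participants (Sample) and about 90 minutes per consent and baseline visit (Procedures).

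25 × 90 min = 2,250 min = 37.5 h.

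This is total visit time, including consent and research data collection. The onboarding share is not given, so 37.5 h is not an estimate of the missing labour.

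**3. Illustrative share of omitted time**

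Let o be onboarding minutes per patient and m pharmacist minutes per patient-week over the 12-week intervention. Both are assumptions.

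Share omitted = o / (o + 12m)

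- Low end, o = 30, m = 30: 30 / (30 + 360) = 0.08.
- Middle, o = 60, m = 10: 60 / (60 + 120) = 0.33.
- High end, o = 90, m = 5: 90 / (90 + 60) = 0.60.

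The omission could be small or more than half of the combined time. Only the missing record would tell.

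**4. Does caseload add to the understatement?**

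With even enrolment of N patients over A weeks, the mean number active at once is 12N / (A + 12).

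- N = 25, A = 0: 300/12 = 25.
- N = 25, A = 12: 300/24 = 12.5.
- N = 25, A = 26: 300/38 = 7.9.
- N = 25, A = 44: 300/56 = 5.4.
- N = 12, A = 44: 144/56 = 2.6.

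The article gives only a recruitment start (November 2016) and an expected end of data collection (late 2017), so anything from about 3 to 25 is possible.

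For direction, let F be fixed weekly pharmacist minutes, v minutes per patient and c the caseload. Time per patient-week is F/c + v. With assumed F = 30 and v = 5:

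- c = 6: 30/6 + 5 = 10.0 min.
- c = 25: 30/25 + 5 = 6.2 min.
- c = 100: 30/100 + 5 = 5.3 min.

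A small caseload raises time per patient, or leaves it unchanged if F = 0. It does not lower it.

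**The case against.** The strongest reply is that the sentence speaks of maintaining the programme. That can be read as the pharmacist's continuing work, with one-off set-up left aside, and the article never promises a total implementation cost. It also describes a preliminary single-group pilot: "We are enrolling up to 25 patient participants for this pilot study". This lowers the importance of the point but does not remove it. Set-up is one-off for a patient but recurs for a programme that keeps enrolling, and nothing limits the personnel result to pharmacist time.

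Second, not all the study-staff work would carry over to a clinic. Readings can be entered by hand without syncing, the monitor check is a comparison rather than a calibration, and nothing says an adopting clinic must repeat it. This stands, and it is a reason to log tasks separately instead of counting whole visits.

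Third, the article is condensed, and a fuller protocol might hold a staff time record. That is possible. The point concerns the source the article itself names for personnel needs; if staff time is already recorded, the text needs only to say so.

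A reader might also infer that the pharmacist oversees only a handful of patients at once and that this too makes the need look low. The documents do not support this. Concurrency is not stated, and fixed time spread over few patients would push per-patient time up, against the claimed direction. Nor does the article force fixed and per-patient work together, since its logs name app time apart from monitoring and follow-up time. Reporting time per active patient-week is a detail an article may leave to fuller documents.

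**Conclusion.** The point holds in a limited form. The article's one stated basis for personnel needs covers the pharmacist, while onboarding is done by study staff whose time it does not plan to record. A personnel estimate drawn from the logs would be a pharmacist-time estimate and would understate total staffing for a clinic that continues to enrol.

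The direction rests on one assumption: that an adopting clinic must do at least part of this onboarding with its own staff. The size cannot be computed from the documents. The 8% to 60% range comes wholly from assumed times and shows only that the omission need not be trivial. It would be wrong to treat the 37.5 hours of baseline visits, or any fixed fraction of them, as the shortfall.

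Nor does the feasibility conclusion as a whole rest on these logs; utilization data, perceptions and interviews also feed it. Severity is minor: a cheap improvement to a pilot, with no bearing on the blood pressure analyses.

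**What to change.** Have study staff record, for each participant, the minutes spent on app installation, app training, monitor set-up (instruction, syncing and check) and later technical help. Keep these apart from consent, surveys and other research data collection. The manual reading needs care, because one is also taken at baseline as a study measure. Report the onboarding and support minutes beside the pharmacist's time when personnel needs are described.

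For participants already enrolled, where the minutes can no longer be recorded, state that the personnel figure covers pharmacist time only, at the caseload seen in the pilot. Any retrospective staff estimate should be labelled as such.

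The cost is one short log entry per visit or help call by staff already doing the work, with no new visits or procedures for participants. Limiting the conclusion costs one sentence.

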### Statistical Analysis Plan

Descriptive statistics will be used to describe patient participant characteristics and perceptions, mHealth utilization, and clinical pharmacist utilization and perceptions. Categorical data will be displayed as frequencies and percentages, and Chi-square tests will be used for comparisons. SBP and DBP will be expressed as mean (standard deviation) and pre/postintervention BP means will be compared using 2-tailed paired samples t-tests.

The effect of clinical pharmacist contact with patient participants will be evaluated through changes in utilization of the mHealth app and changes in BP levels surrounding the time of contact. Models will be used to separately evaluate SBP and DBP levels over time, including pharmacist contact as a time-varying covariate using a mixed-effects regression approach. The mixed-model analysis accounts for the correlation of BP measures on the same individual across time. Similar analyses will be carried out on daily utilization of the mHealth app. Daily usage will be coded as a binary response and modeled using generalized estimating equations, including pharmacist contact with patient participants as a covariate to identify the odds of app usage before and after contact.

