## Methods

### Overview

We are currently conducting a 12-week pre/postintervention pilot study of BPTrack, a clinical pharmacist-led mHealth intervention, which seeks to improve BP control among uncontrolled hypertensive patients recruited from a primary care setting, and who are receiving treatment for their HTN under the care of a clinical pharmacist embedded in the primary care clinic. The final protocol closely mirrored what was originally proposed to the funder (see Multimedia Appendix 1 and Multimedia Appendix 2 for original review scoring forms). The methods for this study have been approved by the University of Michigan IRBMED Institutional Review Board (HUM00105772).

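### Unqualified chi-square tests do not suit one pre/post group of at most 25: paired comparisons need McNemar's test, and sparse subgroup tables an exact test or description only

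*Protocol article*

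**What the plan says.** The Statistical Analysis Plan section of the protocol article gives one rule for categorical data: "Categorical data will be displayed as frequencies and percentages, and Chi-square tests will be used for comparisons". It does not list the comparisons or qualify the test. The one repeated binary outcome that it names is treated separately: "Daily usage will be coded as a binary response and modeled using generalized estimating equations".

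For continuous BP the same section respects the pairing: "pre/postintervention BP means will be compared using 2-tailed paired samples t-tests". It adds mixed models for BP over time.

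The Overview calls the study a "12-week pre/postintervention pilot study of BPTrack". On size, the Sample section says: "We are enrolling up to 25 patient participants for this pilot study". The Limitations section acknowledges that there is no comparison group and argues that "our single group design is warranted". To be eligible, patients must "have uncontrolled HTN (SBP >140 mmHg and/or DBP >90 mmHg on repeat measurements".

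**The concern.** With no second arm, a categorical comparison between time points or between kinds of patient takes one of two forms.

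- **Before versus after in the same patients.** The ordinary chi-square test assumes independent observations, which these are not.
- **Between subgroups of 25 or fewer patients.** The usual condition that every expected count is at least 5 will rarely be met, and no fallback is given.

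The section allows for within-patient dependence in its paired t-tests, mixed models and GEE, but not in the categorical sentence. A pre/post comparison of BP category or control is a realistic possibility: Table 1 sorts BP into categories, and Comparison to Prior Work reports an earlier trial by percentage controlled. At stake is a p-value that could mislead in either direction in data meant to inform later work.

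**Working it through.** **Inputs from the article.** One group; at most 25 patients; measured before and after 12 weeks; chi-square for categorical comparisons; baseline control near zero by eligibility. **Assumed here:** two-sided alpha 0.05, outcome rates, within-patient correlations, subgroup splits.

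**The plan's own figure.** There is no power calculation to reproduce. The size is pragmatic, and the Limitations section says: "Our intended sample size is large enough to satisfy the rule of thumb of 12 participants per group". 25 exceeds 12, so that statement is met. It does not bear on the choice of test.

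**Step 1. Paired example with a non-zero baseline.** Treat 25 before and 25 after as independent. With *k* the rise in the number controlled and *m* the total controlled over both times, Pearson's statistic reduces to

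X² = 50k² / [m(50 − m)].

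The exact McNemar p-value uses only the discordant pairs. With all *k* changes in one direction it is 2 × 0.5^k. For k = 6 this is 2 × 0.5⁶ = 0.031, whatever the baseline.

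| Before to after | X² | Pearson p | Exact McNemar p |
|---|---|---|---|
| 0 to 6 | 1800/264 = 6.82 | 0.009 | 0.031 |
| 3 to 9 | 1800/456 = 3.95 | 0.047 | 0.031 |
| 6 to 12 | 1800/576 = 3.13 | 0.077 | 0.031 |
| 8 to 14 | 1800/616 = 2.92 | 0.087 | 0.031 |

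The same six changes give Pearson p-values on both sides of 0.05, depending on the baseline.

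**Step 2. Paired example with a zero baseline.**

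- 0 to 4: X² = 800/184 = 4.35, p = 0.037; exact McNemar 2 × 0.5⁴ = 0.125.
- 0 to 5: X² = 1250/225 = 5.56, p = 0.018; exact McNemar 2 × 0.5⁵ = 0.063.

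Here the smallest expected counts are m/2 = 2 and 2.5, so small counts drive much of the gap.

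**Step 3. Error rate and power for 25 pairs, by full enumeration.** The first three rows assume a 50% rate at both times (type I error). The last two assume a rise from 40% to 70% (power).

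| Case | Correlation | Pearson | McNemar chi-square | Exact McNemar |
|---|---|---|---|---|
| Type I error | 0.3 | 0.027 | 0.043 | 0.021 |
| Type I error | 0.5 | 0.009 | 0.048 | 0.014 |
| Type I error | 0.7 | 0.001 | 0.041 | 0.004 |
| Power | 0.3 | 64% | 70% | 59% |
| Power | 0.5 | 66% | 91% | 77% |

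Away from a zero baseline, ignoring positive correlation is mainly conservative. The exact test is conservative too, and at correlation 0.3 it has slightly less power than Pearson.

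**Step 4. Expected counts in a 2×2 subgroup table.** The smallest expected count is r × c / n, with r and c the smaller row and column margins. For n = 25 it reaches 5 only if r × c ≥ 125. Since 12 × 12 = 144 and 11 × 12 = 132 pass, while 11 × 11 = 121 and 10 × 12 = 120 fail, only margins 12 and 12, or 11 and 12, qualify. For n = 20, r × c ≥ 100 leaves only 10 and 10.

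**Step 5. Pearson type I error in such tables, by enumeration.**

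| Split | Rate 50% | 30% | 20% | 10% | 5% |
|---|---|---|---|---|---|
| 12/13 | 0.045 | 0.052 | 0.049 | 0.018 | 0.003 |
| 8/17 | 0.045 | 0.048 | 0.051 | 0.045 | 0.026 |
| 5/20 | 0.056 | 0.045 | 0.047 | 0.076 | 0.090 |

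The 8/17 split never meets the expected-count rule, yet its error stays near 0.05 at rates from 10% to 50%. Fisher's test in the 5/20 split gives 0.015 at 10% and 0.009 at 5%.

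**The case against.** **No categorical pre/post comparison is named.** Patient characteristics are collected at baseline only and perceptions at 12 weeks only. The measures taken at both times are clinic BP, the ARMS and a pill-count percentage. This stands, so the paired fault is conditional on such a comparison being run.

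**Chi-square could include McNemar's chi-square.** The text does not say so. That reading would cure the pairing but not the small counts: four changes against none gives 4²/4 = 4, p = 0.046, against 0.125 exactly.

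**The examples pull against each other.** If eligibility fixes baseline control near zero, the loss-of-power cases do not apply to BP control. That is fair. For BP control the zero-baseline cases are the relevant ones. The others concern a categorical outcome, such as a finer BP category, that is not fixed at entry.

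**A condensed article may leave detail to a fuller plan.** That excuses the missing list of comparisons. It does not excuse an unqualified test that fits the design poorly.

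**Stronger readings that a reader might infer.** One is that every chi-square p-value here would be invalid; Step 5 does not support that. Another is that the study's main aim rests on this test. The Study Objective is feasibility and acceptability. Improving BP control describes what the intervention seeks, and the BP effect is planned on means and mixed models.

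**Conclusion.** The point holds in a limited form. Apart from daily app use, the plan assigns chi-square tests to categorical comparisons without qualification, in a design where those comparisons are either paired or made in small subgroups.

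For paired data the test of independence is the wrong test. It is usually conservative under positive correlation (0.087 against 0.031 for 8/25 to 14/25) and overstates the evidence from a zero baseline (0.037 against 0.125 for 0/25 to 4/25). For subgroups, type I error was off in sparse or unbalanced tables (0.003 to 0.090) and near 0.05 in many others.

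These sizes rest on the assumed rates, correlations and splits, and the two paired examples assume that all changes go one way. The point should be fixed but is of modest weight, because no named objective depends on a chi-square result.

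**What to change.** Replace the chi-square sentence with one stating that paired categorical comparisons use McNemar's test in its exact form, and that subgroup tables with small expected counts use Fisher's exact test or are described without a test.

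If BP control is reported, give the 12-week proportion with an exact 95% confidence interval. A test against baseline would compare with a value that eligibility sets near zero. This need not become a main result, since the plan does not define such an endpoint.

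The cost is one or two sentences, with no change to data collection or sample size. The drawback is that exact tests are somewhat conservative at this size, as Steps 3 and 5 show.

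### The BP models for pharmacist contact name no adjustment for physician visits, so part of any fall after a nearby visit can be credited to the pharmacist

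*Protocol article*

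**What the plan says.** The Statistical Analysis Plan section of the protocol article gives the aim: "The effect of clinical pharmacist contact with patient participants will be evaluated through changes in utilization of the mHealth app and changes in BP levels", looking at the period around each contact. Separate mixed-effects models address "SBP and DBP levels over time, including pharmacist contact as a time-varying covariate". No other time-varying exposure is named for these models, and none is expressly ruled out.

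Three other sections bear on the point.

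- **Sample:** each participant must "be under the care of a primary care physician at the recruiting clinic", so physician care runs alongside pharmacist care throughout.
- **Procedures:** patients are told that "if BP readings exceed these critical thresholds for three days in a row, they should contact the clinic". In the same section, readings that stay elevated lead the pharmacist to contact the patient and to decide whether a clinic visit is needed.
- **Health Care Utilization:** a retrospective chart review will "document the number and reason for primary care visits during the course of this study". It covers pharmacist contacts and also those "with a primary care physician at the recruiting clinic, and the Emergency Department at the academic medical center". Number, reason, frequency and nature are listed; dates are not.

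The Limitations section concedes the lack of a control group and of adequate power. It does not mention concurrent physician care.

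**The concern.** With a single group, the pre/post t-test can only describe the whole programme. The contact coefficient in the mixed models is the one planned blood pressure estimate that tries to isolate what pharmacist contact adds.

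A physician visit is a competing exposure: it may change treatment and so lower blood pressure. If visits tend to fall near pharmacist contacts and the model has no term for them, the contact coefficient picks up part of the physician's effect. The documented procedures give a reason to expect some overlap, since elevated readings can start both pathways. The physician contacts are already to be abstracted, yet the article states no use of them in these models.

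The pilot is meant to supply preliminary data for planning later work. A coefficient that mixes the two sources of care could mislead that planning about the value of the pharmacist component.

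**Working it through.** The plan states no figure on this point, so there is none to reproduce. The check is of the mechanism and its size.

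**Inputs from the document:** up to 25 patients (Sample); 12 weeks, so 12 × 7 = 84 days (Procedures); contact as a time-varying covariate in a mixed model (Statistical Analysis Plan).

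**Inputs assumed, because the document gives none:** the blood pressure fall after a physician visit, the share of visits and contacts that lie close together, and the size and serial correlation of day-to-day variation. The true pharmacist effect is set to zero throughout.

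**Formula.** Let c = 1 after the contact and v = 1 after the physician visit. Suppose SBP = patient level + βc·c + βv·v + γ·day + error. If v is left out, the expected contact coefficient is βc + βv·δ, where δ is the slope on c when v is regressed on c, day and patient. With βc = 0, the false effect is βv·δ. It is zero if visits do not lower blood pressure (βv = 0) or are unrelated in time to contacts (δ = 0).

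**Simulation A.** Random-intercept model with study day; patient SD 10 and day SD 7 mmHg; lag-1 correlation 0.3; 80% of patients contacted once at random times; 25% background physician visits; 60 runs per scenario. Coefficients in mmHg:

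| Contacts with a visit within 7 days | Visit effect | Contact only | Visit term added | Implied δ |
|---|---|---|---|---|
| 20% | -4 | -0.51 | 0.13 | 0.51/4 = 0.13 |
| 20% | -8 | -1.04 | -0.10 | 1.04/8 = 0.13 |
| 40% | -4 | -1.20 | -0.05 | 1.20/4 = 0.30 |
| 40% | -8 | -2.53 | -0.02 | 2.53/8 = 0.32 |
| 60% | -4 | -1.91 | -0.06 | 1.91/4 = 0.48 |
| 60% | -8 | -3.58 | 0.08 | 3.58/8 = 0.45 |

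For a given overlap the implied δ hardly depends on the visit effect, as the formula predicts.

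**Simulation B.** Within-patient regression with linear time; within-patient SD 8 mmHg; lag-1 correlation 0.6; one contact and one visit per patient; 150 runs per scenario. Contact-only coefficients in mmHg:

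| Visits placed within 7 days of the contact | Visit effect -3 | Visit effect -5 | Visit effect -8 |
|---|---|---|---|
| None deliberately | -0.01 | -0.17 | 0.06 |
| Half | -1.14 | -1.76 | -2.93 |
| All | -2.24 | -3.72 | -5.89 |

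At full overlap, 2.24/3 = 0.75, 3.72/5 = 0.74 and 5.89/8 = 0.74, so about three quarters of the visit effect goes to the pharmacist. With the visit term added, the mean coefficient lies between -0.12 and 0.15 in every scenario.

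**Simulation C.** A separate run with random contact times gave about -0.6 to -3.7 mmHg at 20 to 60% overlap and about zero with none.

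**Contact triggered by high readings.** This is what Procedures describes. In B, with triggered contacts and no visit effect, the coefficient is 0.87 with or without the visit term, so this is a separate bias. With a visit effect of -5 and half the visits near, it is -0.94 without the term and 0.80 with it. The two biases roughly add: 0.87 - 1.76 = -0.89. In C, when high readings triggered both contacts and visits, the coefficient was about -1.1 to -3.2 mmHg without the term (visit effect 4 to 8 mmHg) and about -0.6 to 1.0 with it.

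**The case against.** The strongest reply is that the article is condensed. The word *including* does not close the list of covariates, and a full plan may hold more. A reader might infer that the plan leaves physician visits out by design. The text does not support that, and all that can be said is that no adjustment is named. What remains is that the stated aim is an effect of contact, one exposure is named for it, and a recorded competing exposure is given no role.

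Second, a reader might infer that visits will cluster around contacts and that the trial will therefore report a pharmacist effect where none exists. The documents do not support this either. They give no rate or timing of physician visits; patients are told to contact the clinic, where the pharmacist also works; and without overlap the bias is about zero. Participants also enter uncontrolled although already under a physician and on medication, so a lasting fall after each visit is not assured. This stands, and the claim is conditional.

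Third, a visit that follows a contact may be a consequence of it, because the pharmacist can bring the patient in. Adjusting for such visits would remove part of a real effect. The simulations count every nearby visit as contamination, so they overstate the bias to the extent that the pharmacist arranged those visits. This also stands, and it shapes the fix.

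Fourth, adjustment does not make the estimate causal, since contact itself depends on earlier readings. In one triggered scenario above it moved the bias from -0.94 to 0.80 mmHg, hardly smaller in size.

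Finally, simulation A rejected at p<0.05 in 27 to 100% of runs without the visit term. That should not be leaned on: with the term, 7 to 17% were still rejected, because the fitted model ignores serial correlation. The bias is the sounder measure.

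**Conclusion.** The point holds in conditional form. The article names no adjustment for physician visits in the blood pressure models for pharmacist contact, although it plans to abstract those visits. If visits lower blood pressure and lie near contacts, part of the fall can be credited to the pharmacist.

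The false effect is about -0.5 to -3.7 mmHg if 20 to 60% of contacts have a nearby visit and a visit lowers SBP by 4 to 8 mmHg, and about zero without overlap. Both inputs are assumptions, and the range takes contacts as randomly timed. Adding the visit term brings the estimate close to zero under that timing. It usually helps, but does not fully correct, when high readings trigger contact.

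The weight is modest. The objective is feasibility and acceptability, this analysis is secondary, and the daily app-use model is a separate analysis that this point does not touch. It is a cheap improvement, not a flaw that undermines the pilot.

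**What to change.** 1. In the existing chart review, abstract the date of each physician visit at the recruiting clinic, along with the reason already planned.
2. Keep the SBP and DBP models as described. As a sensitivity analysis, add physician visits as a second time-varying covariate, coded in the same way as pharmacist contact.
3. Use the recorded reason to identify visits the pharmacist arranged, and leave those out of the physician term so that they stay inside the pharmacist effect.
4. Report the contact coefficient with and without the physician term.
5. Describe the coefficient as an association in both versions, because contact is also prompted by elevated readings.

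The cost is one more field in a review already planned and one more covariate. Intervals will be slightly wider: in simulation B the SD of the adjusted coefficient was 1.04 to 1.15 mmHg with no deliberate overlap and 1.49 to 1.53 when every visit lay near the contact. Deciding which visits the pharmacist arranged takes some judgement, which is why both versions should be shown.
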